## Abstract

**Background:**

Testicular cancer (TC) survivors have an increased risk of various second primary malignancies. A recent cohort study detected an increased risk of colorectal cancer (CRC) in TC survivors treated with platinum-based chemotherapy with a hazard ratio of 3.9. CRC risk increased with higher cisplatin-dose. We know that colonoscopy surveillance in high-risk populations results in reduced incidence and mortality of CRC. TC survivors treated with platinum-based chemotherapy can potentially benefit from colonoscopy surveillance; however, to which extent is unknown. Furthermore, the pathogenesis of these secondary CRCs is unknown, and better insights into the carcinogenesis may affect surveillance decisions.

**Methods:**

This prospective multicenter study will be performed in four Dutch hospitals. TC survivors are eligible if treated with ≥ 3 cycles of cisplatin before age 50. Colonoscopy will be performed ≥ 8 years after initial treatment (minimum and maximum ages at colonoscopy, 35 and 75 years, respectively). The primary aim of the study is the diagnostic yield of advanced neoplasia detected during colonoscopy. As secondary aim, we will evaluate the molecular profile of advanced colorectal neoplasia and will assess current platinum levels in blood and urine and correlate blood-platinum levels with prevalence of colorectal lesions. Furthermore, we will investigate effectiveness of fecal immunochemical testing (FIT) and burden of colonoscopy by two questionnaires. Demographic data, previous history, results of colonoscopy, hemoglobin level of FIT and results of molecular and platinum levels will be obtained. Yield of colonoscopy will be determined by detection rate of adenoma and serrated lesions, advanced adenoma detection rate and CRC detection rate. The MISCAN model will be used for cost-effectiveness analyses of CRC surveillance. With 234 participants undergoing colonoscopy, we can detect an absolute difference of 6% of advanced neoplasia with 80% power.

**Discussion:**

TC survivors treated with cisplatin-based chemotherapy can benefit from CRC surveillance. Evaluation of the diagnostic performance and patient acceptance of CRC surveillance is of importance to develop surveillance recommendations. Insight into the carcinogenesis of cisplatin-related advanced colorectal lesions will contribute to CRC prevention in the increasing number of TC survivors. The results may also be important for the many other cancer survivors treated with platinum-based chemotherapy.

***Trial registration*:**

Clinical Trials: NCT04180033, November 27, 2019, https://clinicaltrials.gov/ct2/show/NCT04180033.

## Background

Due to improved treatment strategies, testicular cancer (TC) survival has strongly increased over the past decades, especially since the introduction of cisplatin-based chemotherapy [1]. As TC usually is diagnosed at a young age, this high cure rate results in a long life-expectancy [2–5]. Yet, this life-expectancy can be compromised by late adverse treatment effects such as second primary malignancies [6].

A cohort study detected an increased risk of developing colorectal cancer (CRC) in TC survivors treated with platinum-based chemotherapy with a hazard ratio of 3.9 compared with the general population [7]. A dose–response relationship between platinum and gastro-intestinal second primary malignancies including CRC has been demonstrated [7]. An increased risk for gastro-intestinal cancers, mainly CRC, pancreatic and gastric cancer, has also been described in childhood cancer survivors treated with platinum-based chemotherapy [8]. Other studies have also reported an increased incidence of CRC following TC treatment with a RR varying between 1.3 and 2.3 compared with the general population [9–15]. The risk of developing CRC remained significantly elevated for a long period after TC treatment with elevated risks reported even after 35 years [12, 13, 16]. Therefore we hypothesize that comparable to other high-risk groups for developing CRC, colonoscopy surveillance may be beneficial in the follow-up of TC survivors [17, 18]. Because colonoscopy is an invasive procedure, surveillance by fecal immunochemical testing (FIT) may be a good alternative. FIT is effective and a non-invasive CRC screening strategy, however, effectiveness in high-risk groups is not known.

Currently, the pathogenesis of CRC in TC survivors exposed to cisplatin is poorly understood. In several studies, platinum was still detectable in serum and urine up to 20 years after treatment [19–21]. Cisplatin can cause DNA damage by inducing crosslinks. Therefore, CRCs and their precursor lesions in TC survivors may differ histopathologically or molecularly from sporadic CRC.

We designed a prospective study to determine the diagnostic yield of advanced neoplasia (advanced adenomas, advanced serrated lesions or CRC) in TC survivors treated with platinum-based chemotherapy as these patients have an increased risk for developing CRC. FIT surveillance is non-invasive and may be a good alternative to colonoscopy surveillance. The accuracy of FIT with regard to the detection of advanced neoplasia will be determined. Furthermore, the burden of colonoscopy and cost-effectiveness of different CRC surveillance strategies will be evaluated. Additionally, the level of platinum in plasma and urine and the histopathological and molecular pattern of advanced neoplasia will be assessed. Insight into the pathogenesis and the association with platinum levels may result in a tailored CRC surveillance program for TC survivors.

## Methods/design

### Objectives

The primary objective of this study is to evaluate the diagnostic yield of advanced colorectal neoplasia by surveillance colonoscopy in TC survivors treated with platinum-based chemotherapy. Advanced neoplasia is defined as advanced adenoma (high-grade dysplasia, > 25% villous component or ≥ 10 mm), advanced serrated lesion (dysplasia or ≥ 10 mm diameter) or CRC [22, 23].

The secondary objectives are to assess the effectiveness of FIT in detecting advanced neoplasia and to examine patient perception (burden, acceptance and satisfaction). We will evaluate which CRC surveillance strategy (FIT or colonoscopy) is most cost-effective in TC survivors. Furthermore, we will evaluate the clinicopathological and molecular characteristics of advanced neoplasia and relate that to platinum level in plasma and urine in TC survivors.

This prospective cross-sectional cohort study was approved by the Medical Ethics Committee of the Netherlands Cancer Institute (Dutch Trial Registry (NL68513.031.19) and registered at Clinical Trials (NCT04180033)) and is currently ongoing.

### Study design

#### Population

TC survivors will be selected from a well-defined multicentre cohort including 5.848 1-year TC survivors who were treated between 1976 and 2007 [7]. Inclusion criteria for this study are as follows: (1) treatment of primary TC should have consisted of ≥ 3 cycles of platinum-based chemotherapy consisting of cisplatin; (2) diagnosis of TC was made before the age of 50 years; (3) initial treatment for TC administered at least 8 years prior to inclusion; (4) the patients should be at least 35 years of age and not older than 75 years of age and (5) detection and potential treatment of advanced colorectal neoplasia should be considered beneficial, i.e. life-expectancy of at least 5 years.

TC survivors are not eligible for participation in this study if they meet one of the following exclusion criteria: a history of proctocolectomy, colonoscopy surveillance for other indications (including hereditary CRC syndrome, familial CRC syndrome, inflammatory bowel disease, history of colorectal adenoma or CRC), colonoscopy in the past 3 years, ongoing cytotoxic treatment or radiotherapy for malignant disease, coagulopathy (prothrombin time < 50% of control; partial tromboplastin time > 50 s) or anticoagulants (fenprocoumon, acenocoumarol, or direct oral anticoagulants) or platelet aggregation inhibitors that cannot be stopped or safely bridged if necessary, comorbidity leading to an impaired physical performance (World health organization (WHO) performance status 3–4) or mental retardation, limited Dutch language skills or no informed consent.

A total of 1.801 men treated in the four different hospitals in the Netherlands could potentially be eligible. Individuals who do meet the inclusion criteria will be invited for participation in one of the four Dutch study centers (Netherlands Cancer Institute, Amsterdam, Erasmus University Medical Center, Rotterdam, Radboud University Medical Center, Nijmegen and University Medical Center Utrecht, Utrecht). The flowchart of the design of this study is shown in Fig. 1. Participants who are eligible for participation will be invited for this study. Referral to the gastroenterology department will occur via the general practitioner or medical oncologist, depending whether the individual is still in follow-up for TC. Informed consent will be concluded by a gastroenterologist or nurse specialist, when the participant was informed adequately.

**Fig. 1 Fig1:**
[figure not shown]
Flowchart of study. Abbreviations: *FIT* Fecal immunochemical test; *TC* testicular cancer

For patients who will be excluded due to colonoscopy in the 3 years prior to invitation we will evaluate the yield of colonoscopy retrospectively. This study was approved by the Institutional Review Board of the Netherlands Cancer Institute (IRBd19-236).

#### Control population

The diagnostic yield of colonoscopy in TC survivors will be compared to the NordICC study. This is a European randomized trial for population-based primary colonoscopy screening for colorectal cancer. Participants were between 55 and 64 years of age and we selected only male participants to compare with our male cohort of TC survivors [24]. For molecular profiling, data will be compared with existing molecular data of colorectal lesions (mainly polyps) diagnosed in Dutch patients before the age of 70 years [25].

#### Sample size calculation

The power calculation is based on the primary endpoint of this study: the diagnostic yield of advanced colorectal neoplasia by screening colonoscopy. The prevalence of advanced colorectal neoplasia in the NordICC study population was 10.3% among the 6,493 male participants who underwent colonoscopy screening (based on the most recent data) [24]. We will use the data from the male participants of the NordICC study aged 55–64 years old and use frequency matching with 5-year strata of the NorcICC male patients to patients in our study. We do believe that colonoscopy surveillance is justified with an increase detection rate of advanced neoplasia adjusted for age of 6%. In order to detect this 6% difference in advanced neoplasia in TC survivors with at least 80% power (using a two-sided alpha of 5%), we need to include at least 234 TC survivors. A margin of 40% will be considered for non-responders and drop-outs based on previous participation rates and therefore 338 men will be approached. An interim analysis will be performed after the inclusion of 100 participants.

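### Age matching to NordICC men aged 55–64 has no controls for survivors aged 35–54 or 65–75, and 234 gives about 80% power only if nearly all participants are 55–64

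*Protocol article*

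**What the plan says.** All references are to the protocol article.

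- **Survivors' ages** (Population): "the patients should be at least 35 years of age and not older than 75 years of age". The Abstract gives the same limits for age at colonoscopy.
- **Comparator's ages** (Control population): "Participants were between 55 and 64 years of age and we selected only male participants to compare with our male cohort of TC survivors". No other comparator for yield is named. The second control source in that section serves molecular profiling only.
- **Age adjustment** (Sample size calculation): "We will use the data from the male participants of the NordICC study aged 55–64 years old and use frequency matching with 5-year strata". The 6% increase held to justify surveillance is described there as age-adjusted.
- **Background rate** (Sample size calculation): "The prevalence of advanced colorectal neoplasia in the NordICC study population was 10.3% among the 6,493 male participants who underwent colonoscopy screening".
- **Claimed power** (Abstract, Methods): "With 234 participants undergoing colonoscopy, we can detect an absolute difference of 6% of advanced neoplasia with 80% power". The Sample size calculation adds a two-sided alpha of 5%.

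Nowhere does the article limit recruitment or the comparison to ages 55–64, or say how many participants are expected to fall in that band.

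**The concern.** Frequency matching sets the age mix of the controls to that of the cases, stratum by stratum. It needs controls in every stratum that holds cases. With NordICC men aged 55–64, that is possible for 55–59 and 60–64 only.

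The sample size treats all 234 survivors as matchable and gives them a single background of 10.3%. The eligibility range, the control range, the matching rule and the stated power therefore cannot all hold.

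This is the only powered comparison in the article, and its 6-point margin is what is said to justify surveillance. If survivors outside 55–64 are left out, power falls. If they are kept and compared with 10.3%, the difference mixes the effect of cisplatin exposure with the gap in age.

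**Working it through.** **Inputs.** Control prevalence p0 = 10.3%, m = 6,493 control men, two-sided alpha 5%, n = 234 survivors (Sample size calculation). The 6 points are absolute (Abstract, Methods), so p1 = 16.3%. The share f of participants aged 55–64 is not given and is varied.

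**Formula** (pooled two-proportion test):

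- pooled rate p̄ = (n·p1 + m·p0)/(n + m)
- SE0 = √[p̄(1−p̄)(1/n + 1/m)]
- SE1 = √[p1(1−p1)/n + p0(1−p0)/m]
- power = Φ[(p1 − p0 − 1.96·SE0)/SE1]

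**Step 1: reproduce the plan.** With n = 234, p̄ = 0.1051, SE0 = 0.0204 and SE1 = 0.0244. Power = Φ[(0.06 − 1.96 × 0.0204)/0.0244] = 79.3%. Reaching 80% takes 239. The one-sample formula against a fixed 10.3%, [(1.96√(0.103×0.897) + 0.842√(0.163×0.837))/0.06]², gives 229. The planned 234 lies between the two, so the arithmetic is sound provided that every survivor is comparable with the full NordICC male set.

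**Step 2: count the strata.** Ages 35–74 form eight 5-year strata, plus the single year 75. NordICC men fill two (55–59 and 60–64). Six of the eight are empty.

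**Step 3: confine the comparison to the overlap.** Same formula, n = 234 × f, all 6,493 controls kept. The last column is 239/f.

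| Share aged 55–64 | Men | Power for +6 points | Difference detectable at 80% | Total needed for 239 in the band |
|---|---|---|---|---|
| 100% | 234 | 79.3% | 6.1 points | 239 |
| 80% | 187 | 71.5% | 6.8 points | 299 |
| 70% | 164 | 66.8% | 7.3 points | 342 |
| 50% | 117 | 54.8% | 8.7 points | 478 |
| 30% | 70 | 39.5% | 11.4 points | 797 |

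With 225 men in the band (about 4% outside it), power is already down to 78.0%.

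**Step 4: what share is plausible?** The article gives treatment between 1976 and 2007, diagnosis before 50, and inclusion expected to finish in June 2022. My assumptions are treatment years spread evenly from 1976, 1985 or 1990 to 2007, age at treatment roughly normal with mean 28–36 and SD 6–9, and examination in 2021. Simulated this way, about 25–45% of eligible men are 55–64. This describes eligible men, not those who accept colonoscopy.

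**Step 5: compare all 234 with 10.3%.** Suppose the age-expected prevalence c of the survivors' age mix is below 10.3% (assumption) and the true excess is 6 points, so that p1 = c + 6%:

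| c | Survivors' true yield | Apparent difference from 10.3% | Power |
|---|---|---|---|
| 7% | 13% | 2.7 points | 28% |
| 8% | 14% | 3.7 points | 45% |
| 9% | 15% | 4.7 points | 62% |

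**The case against.** **234 is correctly calculated.** This stands. It would be wrong to read the point as an arithmetic error. The loss of power depends on how many participants fall outside 55–64 and on how they are handled, and the article never says that they will be dropped.

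**No age distribution is given.** This also stands. A reader might infer that most of the eligible men have no comparator. As a statement about strata (six of eight) that is fact. As a headcount it rests on the assumptions in Step 4.

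**Other analyses exist.** A reader might infer that the only choices are to drop men or to compare crudely. Age-adjusted regression on all men is a third route, and an unseen analysis plan may specify it. But outside 55–64 such a model extrapolates the control age trend with no control data, and it is not the matching that the article describes. An analysis plan can choose a model. It cannot supply NordICC men of other ages.

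**Younger survivors might make the task easier.** If controls of the right ages existed and had lower prevalence, an absolute 6 points would be easier to detect. For example, 6% against 12% with 6,493 controls gives 90.8% power at 234. That is correct, but no such controls are named.

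**The primary objective needs no control.** This stands. The Objectives section asks for the diagnostic yield, which all 234 men can provide (about ±4.7 points at 16.3%, from 1.96√(0.163×0.837/234)).

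**Conclusion.** The concern holds for the external comparison. The age ranges, the matching rule and the stated power contradict one another, and nothing in the article reconciles them. The mismatch is certain. Its cost is conditional.

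For an analysis of the overlap, power is about 72% if 80% of participants are 55–64 and about 40% if 30% are. The assumed 25–45% share points to the lower part of that range. For a crude comparison of everyone with 10.3%, power for a true 6-point excess is 28–62% if the age-expected prevalence is 7–9%.

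A reader might also infer that the crude comparison could produce a false excess. An older age mix could do so in principle, but the article gives no ages to show it, and the figures above cover only the opposite case, an excess that is hidden.

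**What to change.** 1. **Define the NordICC comparison as survivors aged 55–64.** Use a risk difference stratified by 55–59 and 60–64 (Mantel–Haenszel or standardised), with all NordICC men in each stratum. Discarding controls to match costs power: with 2,000 kept, power at 234 falls to 76.0%.
2. **Report yield for 35–54 and 65–75 by age band with confidence intervals**, as descriptive results. The overall yield in all participants stays as planned.
3. **Restate power and detectable difference** in the Abstract and the Sample size calculation for the number expected, or already enrolled, at 55–64.

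The alternative is to name a comparator that covers the other ages and recompute with stratum-specific prevalences.

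The cost is a change of wording and a less favourable power figure.

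Inviting by age stratum is optional and has a real price. It leaves few or no men in the other bands, although the study is meant to support recommendations for men eligible from 35. It may also not reach 239. A 25–45% share of the 1,801 is about 450–810 men. At the 21% and 40% participation rates quoted in the Discussion, that yields about 95–170 and 180–324. At the planning rate of 234/338 = 69%, it yields about 312–561. Recruitment was also already under way.

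An observed-to-expected analysis based on MISCAN should not be added unless the model is shown to supply age-specific prevalence. The Cost-effectiveness analysis section describes it as taking prevalence from this study.

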## Discussion

In this prospective study, TC survivors treated with platinum-based chemotherapy will be offered a colonoscopy in order to evaluate the diagnostic yield in detecting advanced neoplasia as we hypothesize that this population benefits from CRC surveillance. This study is currently ongoing and we expect to complete inclusion in June 2022.

Colonoscopy reduces the risk of CRC and CRC related mortality [31–33]. CRC screening programs for the general average-risk population have been implemented in many countries [24, 34]. There are different CRC screening modalities including primary colonoscopy screening and fecal occult blood test screening with colonoscopy in case of a positive test result. For high-risk-groups a more intensified surveillance program is recommended, and the interval used differs between the different high-risk-groups [18, 35]. For individuals with a family history of CRC and an estimated increased risk of CRC of 2.5 compared to the general population, colonoscopy surveillance is advised every 5 years from the age of 45 years [17, 18]. During colonoscopy precursor lesions of CRC can directly be removed which has been shown to reduce CRC incidence and mortality in high-risk-groups [31, 36–39]. TC survivors treated with platinum-based chemotherapy do have a 3.9-fold increased risk. Due to the increased CRC risk, we will evaluate the diagnostic yield of colonoscopy surveillance. The diagnostic yield of advanced neoplasia detected during colonoscopy in TC survivors will be compared to the male population of the NordICC study, which contains males with an average risk for developing CRC [24].

The participation rate of CRC surveillance is of great importance to benefit as many TC survivors as possible. Currently, most TC survivors are unaware of the increased risk of developing CRC. In a Dutch pilot study with primary colonoscopy screening the participation rate of colonoscopy was only 21% [34]. On the other hand, colonoscopy participation in a high risk group of familial risk was reported between 40% [40]. Therefore, FIT surveillance should be considered, as FIT is less invasive than colonoscopy and therefore could increase the participation rate in CRC surveillance. There are already studies showing that FIT surveillance may be beneficial in different risk groups for CRC by choosing a low cut-off [41]. However, in familial colorectal cancer and other patients with an increased risk of CRC, the accuracy of FIT is unknown.

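### The 338 men to be approached do not follow from 234 participants and a 40% loss, which needs 390; 338 covers a loss of only 30.8%

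*Protocol article*

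**What the plan says.** The Sample size calculation section of the protocol article sets the target: "we need to include at least 234 TC survivors". This number is to detect a 6% increase in advanced neoplasia with at least 80% power at a two-sided alpha of 5%. The Abstract makes clear that the 6% is an absolute difference. The reference rate is "10.3% among the 6,493 male participants who underwent colonoscopy screening". The same section then moves from men needed to men invited: "A margin of 40% will be considered for non-responders and drop-outs based on previous participation rates and therefore 338 men will be approached".

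Two other places bear on this:

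- **Population section.** It describes the pool: "A total of 1.801 men treated in the four different hospitals in the Netherlands could potentially be eligible".
- **Discussion.** It quotes two participation rates from other settings. In a Dutch primary colonoscopy screening pilot, "the participation rate of colonoscopy was only 21" per cent. For people at familial risk, "colonoscopy participation in a high risk group of familial risk was reported between 40" per cent, where the range has no upper end.

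**The concern.** The sentence presents 338 as the consequence of two figures, 234 and 40%, but those figures do not produce it. The margin is meant for people who are approached and do not end up examined, so it is a fraction of those approached. The number to approach is then the target divided by the fraction retained. Adding 40% to the target does not offset losing 40% of those invited.

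What is at stake is the number of colonoscopies available for the primary endpoint. If 338 is used as the recruitment plan and the margin proves right, the study ends below its own stated minimum. A separate question is whether 40% is a reasonable loss at all. The section says that it rests on earlier participation experience, but it neither names nor references that experience.

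**Working it through.** **Inputs**

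- Target: 234 men (Sample size calculation).
- Margin for non-response and drop-out: 40% (same section).
- Men to be approached: 338 (same section).
- Control rate 10.3% in 6,493 men, with an absolute increase of 6 points to 16.3%; two-sided 5%; 80% power (same section, and the Abstract for the word absolute).
- Participation rates quoted in the Discussion: 21%, and 40% from a truncated range.
- Pool: 1,801 potentially eligible men (Population).

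**Step 1. Can 338 be reproduced?**

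- Loss as a fraction of those approached: N/(1 − d) = 234/0.60 = 390. The stated figure is 390 − 338 = 52 lower, which is 52/390 = 13%.
- Margin added to the target, a common mistake: 234 × 1.40 = 327.6, so 328. The stated figure is 10 higher. That is close, but not equal.
- Solving for the loss that 338 allows: 1 − 234/338 = 30.8%.

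Neither way of applying 40% gives 338.

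**Step 2. What does 338 deliver at the plan's own margin?**

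338 × 0.60 = 202.8, so about 203 men examined. The shortfall is 234 − 203 = 31.

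**Step 3. Power at 234 and at 203**

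The comparison is of two proportions, with a pooled variance under the null and all 6,493 controls used:

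power = Φ[(0.06 − 1.96 × SE0)/SE1], where SE0 = √[p̄(1 − p̄)(1/n + 1/6,493)] and SE1 = √[0.163 × 0.837/n + 0.103 × 0.897/6,493].

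| n | p̄ | SE0 | SE1 | z | Power |
|---|---|---|---|---|---|
| 234 | 0.1051 | 0.0204 | 0.0244 | 0.82 | 79.3% |
| 203 | 0.1048 | 0.0218 | 0.0262 | 0.66 | 74.4% |

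This formula needs 239 men for 80% power. A one-sample normal approximation against a fixed 10.3% needs 229 and gives 80.8% at 234 and 75.9% at 203. The plan's 234 lies between the two requirements, so it is reproduced to within rounding and choice of method. Either way, going from 234 to 203 costs about 5 percentage points of power.

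**Step 4. Secondary check, under an assumption**

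A 40% loss implies 60% participation. Suppose instead that one of the Discussion's rates applied to this cohort:

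| Participation | Men to approach for 234 | Men examined if 338 approached |
|---|---|---|
| 60% (implied by the margin) | 234/0.60 = 390 | 203 |
| 40% | 234/0.40 = 585 | 338 × 0.40 = 135 |
| 21% | 234/0.21 = 1,114.3, so 1,115 | 338 × 0.21 = 71 |

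All three numbers to approach are below 1,801.

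**The case against.** The strongest reply is that the power statement attaches to men examined, not men invited. The Abstract ties the 80% to 234 participants undergoing colonoscopy, and the target is 234 included. Nothing says that invitations stop at 338, and the pool covers every scenario above. This stands. The error is a miscounted invitation number, and the loss of power is conditional on stopping at 338. It does not rescue the sentence, which still derives a number that its own inputs do not give.

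A second reply is that 338 may be 328 with a one-digit slip. That is possible, but the documents do not show it. It would also leave the same problem, since 328 is the wrong inflation for a loss.

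A third reply concerns the power figures. The plan intends frequency matching in 5-year age strata, so the usable number of controls may be below 6,493. This stands too, and the 74% is therefore stated as an assumption.

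A reader might go further and infer the following, none of which the documents support:

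- **That the 40% margin contradicts the article's own participation rates.** The sample size section does not name its source. The Discussion's rates come from other populations, are used there to argue about uptake of a future programme, and one is a range without an upper end. The 60% implied by the margin could lie inside that range.
- **That a 40% participation rate was mistaken for a 40% loss rate.** The coincidence of figures is visible, but this would be a guess at the authors' reasoning.
- **That the Population section conflicts with 338.** It calls the 1,801 men only potentially eligible. A pool of that size and a planned approach to 338 can coexist.

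**Conclusion.** The point holds for the recruitment figure. As written, 338 is wrong: a 40% loss requires 390, and 338 is sufficient only if the combined loss is no more than 30.8%. This follows from the Sample size calculation section alone.

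The consequence is conditional. If recruitment ended at 338 and the 40% margin proved right, the study would examine about 203 men. Power would be about 74%, against 79.3% at 234 by the same method. This assumes that all 6,493 controls are used and that the rates are 10.3% and 16.3%.

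The lower participation rates support a request for justification, not a finding of contradiction. The range of 585 to 1,115 approaches holds only if those rates carry over to this cohort. The target of 234, the endpoint and the comparison are unaffected, and the study remains feasible.

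**What to change.** In the Sample size calculation section:

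1. Replace 338 with 390 if a 40% loss is meant. If 338 is meant, state the loss it actually allows for, 30.8%, and give its source.
2. Add that invitations continue from the pool of 1,801 potentially eligible men until 234 colonoscopies have been done, so that 234 is the binding number and the count of invitations is an estimate.
3. Name the earlier participation experience behind the margin. Say in one sentence why about 60% participation is expected here, given the 21% and the 40% quoted in the Discussion, and complete the truncated range there.

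The cost is a corrected sentence or two and more invitation letters: 52 more at a 40% loss, and more if participation is lower. The number of colonoscopies does not change, and nothing in this point calls for a change in how men are sampled for invitation.
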